#### **Secondary Endpoints**

- Unplanned interventions: The number of unplanned interventions required by caregivers during the NIV session will be documented.
- Changes in respiratory and cardiovascular parameters: These parameters will be assessed before the NIV session, immediately after proper setup (5 minutes), and then at hourly intervals (h1, h2, h3, h4):
  - Respiratory rate (RR)
  - Peripheral oxygen saturation (SpO2)
  - Tidal volume (Vt)
  - Leak rate
  - Heart rate (HR)
  - Systolic blood pressure (SBP)
  - Diastolic blood pressure (DBP)
- Respiratory comfort: assessed using a digital visual scale, changes in respiratory comfort will be measured (h0, h2, h4).
- Neurological assessment (h0, h2, h4):
  - Encephalopathy score (Kelly-Matthay scale)
  - Glasgow Coma Scale

- Richmond Agitation-Sedation Scale (RASS)
- Patient-reported outcomes (h0, h2, h4):
  - Borg Dyspnea Scale (BDS)
  - Verbal Numeric Rating Scale (VNS) for pain assessment
- Psychological assessment (h0, h4):
  - Rapid Clinical Test For delirium (4 AT)
  - State Trait Anxiety Inventory (STAI)
  - Spielberger's trait anxiety inventory
  - Perceived stress scale (PSS)

#### Statistical analysis and expected results

The statistical analysis will be conducted using SPSS version 20. All continuous variables will be expressed as mean  $\pm$  SD or median with interquartile range (IQR) (25th-75th percentile), depending on the normality of distribution assessed by the Shapiro-Wilk test. Categorical variables will be summarized as frequencies and percentages.

For the primary endpoint, the mean reduction in PCO2 between the intervention (music therapy) and control groups ( $\Delta$ PCO2= baseline PCO2 – endpoint PCO2) will be compared using a student t-test or Mann-Whitney U test, as appropriate. Repeated measures analysis of variance (ANOVA) or a mixed-effects model approach will be used to analyze within-group changes across time points (h1, h2, h3, h4) ensuring adjustments for potential correlations within repeated measures.

For secondary outcomes:

- Respiratory and cardiovascular parameters: Differences between groups over time will be analysed using repeated measures ANOVA or mixed-effects models.
- Respiratory comfort and patient-reported outcomes (e.g., BDS, VNS): group comparisons will be performed using t-tests or Mann-Whitney U tests for continuous variables, with effect sizes and 95% confidence intervals reported.
- Neurological and psychological assessments: changes from baseline (h0) to endpoint (h4) will be analysed

using paired t-tests or Wilcoxon signed-rank tests within groups, and independent t-tests or Mann-Whitney U tests between groups.

- For categorical secondary outcomes (e.g., unscheduled interventions): comparisons between groups will be made using a chi-square test or Fisher's exact test where appropriate.

Missing data will be handled using multiple imputation techniques if the proportion of missing data is significant, ensuring unbiased estimates. Sensitivity analyses will be performed to assess the robustness of the results, particularly for the primary outcome.

All statistical analyses will be conducted on an intention-to-treat basis at a bilateral 5% alpha risk. Results will be interpreted with both statistical significance ( $p < 0.05$ ) and clinical relevance considered. Analyses will be performed by an independent investigator blinded to treatment allocation, ensuring unbiased interpretation of the data.

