#### **Sampling procedure**

Randomization: All inclusion and exclusion criteria will be thoroughly reviewed. Eligible participants will then be randomly allocated in a 1:1 ratio to either the intervention group (music) or the control group using a computer-generated random sequence to ensure allocation concealment and minimize selection bias.

Blinding of the participants is not possible due to the nature of the intervention; however, primary outcome assessors and data analysts will be blinded to group allocation to reduce assessment and analysis bias according to the prospective randomized open blinded endpoint (PROBE) method.

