#### **Sample size:**

the final sample size is set at 38 patients per group in either a 'musical intervention' group or a 'control' group,

Recruitment is planned over a 6-month period, with a target enrolment of 76 participants.

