#### **Primary Endpoint**

The primary outcome of the study will be the efficacy of NIV measured by the reduction in arterial Pressure of Carbon dioxide (PCO2). This will be calculated as the difference between baseline PCO2 and the PCO2 levels recorded at specific time points during the NIV session (h2, h4):  $\Delta PCO_2 = \text{Baseline } PCO_2 (t_0) - \text{Endpoint } PCO_2 (t_1, t_2)$ .

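### The primary PCO2 comparison is valid but not adjusted for baseline, and it allows, with no stated rule, a test that does not compare the mean reduction it names

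*Protocol*

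**What the plan says.** The Primary Endpoint section defines the outcome as a change score: "This will be calculated as the difference between baseline" PCO2 and the PCO2 at later points in the NIV session, h2 and h4.

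Under Statistical analysis and expected results, the mean reductions in the two arms "will be compared using a student t-test or Mann-Whitney U test, as appropriate". No baseline covariate is named. The next sentence offers a repeated-measures ANOVA or mixed model, but for changes within each group, so it supplies no baseline-adjusted contrast between arms.

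The only distributional criterion in that section concerns presentation. Continuous variables are summarised as mean and SD or as median and IQR, "depending on the normality of distribution assessed by the Shapiro-Wilk test". The text does not say that this check also selects the primary test.

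For comfort and patient-reported outcomes (dyspnoea, pain), "group comparisons will be performed using t-tests or Mann-Whitney U tests for continuous variables". These are recorded at h0, h2 and h4, and again no baseline adjustment is named.

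On size and error rate: "the final sample size is set at 38 patients per group", allocated 1:1, and "All statistical analyses will be conducted on an intention-to-treat basis at a bilateral 5% alpha risk".

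**The concern.** There are two separate weaknesses.

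**Precision.** Subtracting baseline fixes its coefficient at 1. If the true slope of follow-up on baseline PCO2 is below 1, the change score over-corrects. Part of the baseline noise stays in the outcome, and any chance difference in baseline PCO2 between arms moves the estimate. In a trial of 76 patients, precision that costs nothing is worth having.

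**What is being estimated.** The sentence sets out to compare a mean reduction and then permits a test that compares something else. Mann-Whitney addresses whether values in one arm tend to exceed those in the other. It agrees with a comparison of means only under further conditions, such as a pure shift between identically shaped distributions. Because the choice is left as appropriate, the quantity behind the primary p-value is not settled before the data are seen.

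**Working it through.** **The plan's own figure.** The 38 per group cannot be reproduced, because the Protocol gives no effect size, SD, power or dropout. It can only be inverted. With two-sided α = 0.05 and 1:1 allocation, the detectable standardised difference is (z₀.₉₇₅ + z_power) × √(2/38):

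- 80% power: (1.960 + 0.842) × 0.2294 = 0.643 SD
- 90% power: (1.960 + 1.282) × 0.2294 = 0.744 SD

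The 80% case is used below only as a reference point.

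**Inputs.** From the Protocol: n = 38 per arm, two-sided 5%. Assumed: ρ from 0.3 to 0.9, equal variance σ² at baseline and follow-up, and 80% power for the change-score t-test.

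**Variances per patient.**

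- Change score: 2σ²(1 − ρ)
- Baseline-adjusted residual: σ²(1 − ρ²) = σ²(1 − ρ)(1 + ρ)
- Ratio, adjusted to change score: (1 + ρ)/2, a saving of (1 − ρ)/2

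**Power after adjustment**, by normal approximation: Φ(2.802/√ratio − 1.960). The number per arm giving the same 80% power is 38 × ratio, rounded up.

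| Assumed ρ | Variance ratio | Saving | Power | Equivalent n per arm |
|---|---|---|---|---|
| 0.3 | 0.65 | 35% | 93.5% | 25 |
| 0.5 | 0.75 | 25% | 89.9% | 29 |
| 0.6 | 0.80 | 20% | 87.9% | 31 |
| 0.7 | 0.85 | 15% | 86.0% | 33 |
| 0.8 | 0.90 | 10% | 84.0% | 35 |
| 0.9 | 0.95 | 5% | 82.0% | 37 |

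The covariate costs one residual degree of freedom (76 − 2 = 74 becomes 76 − 3 = 73), which this approximation ignores.

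**Without equal variances.** Let β be the slope of follow-up on baseline. The change-score variance exceeds the residual variance by (1 − β)² × Var(baseline). The gain is therefore zero at β = 1 and positive otherwise, and it may be smaller or larger than the table shows.

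**Chance imbalance.** If the arms happen to differ by b in mean baseline PCO2, the change-score estimate is shifted by (1 − β)b, given that imbalance. The SD of b is σ√(2/38) = 0.229σ. With equal variances and ρ = 0.5 (so β = 0.5), a one-SD imbalance shifts the estimate by 0.5 × 0.229σ = 0.115σ. Averaged over randomisations the shift is zero.

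**Test choice.** To see what a data-driven choice could do, suppose that Shapiro-Wilk in each arm decided the test. This is an assumption, since the Protocol does not say so. Simulation at 38 per arm, 6,000 runs per scenario:

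| Both arms drawn from | Mann-Whitney used | Two-stage type I error |
|---|---|---|
| Normal | 10% | 5.4% |
| t, 5 df | 51% | 4.8% |
| Gamma, shape 4 | 81% | 5.2% |
| Lognormal, log-SD 0.5 | 96% | 4.8% |

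With equal means and SDs but one arm normal and the other a shifted exponential, Mann-Whitney is used in 99% of runs. The two-stage procedure then rejects in 8.9%, against 5.1% for the t-test alone. The mean difference is zero in that scenario, so the gap shows that the two tests answer different questions.

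**The case against.** The strongest reply is that nothing here is an error. The change score does use baseline, and randomisation makes the t-test on it unbiased with the right type I error. Chance imbalance matters only conditionally and is already reflected in the standard error. All of this stands. A reader might infer that baseline PCO2 is discarded or that the estimate is biased; the Primary Endpoint definition and the 1:1 randomisation do not support either reading.

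A reader might also infer that Shapiro-Wilk decides the primary test. That is a natural guess, but the text ties it only to how variables are summarised. Even if it did decide, type I error stayed between 4.8% and 5.4% when the arms shared a distribution, and the 8.9% comes from a constructed case. Inflated false positives are therefore not shown. Blinding of the analysts also limits deliberate steering of the choice. It does not settle which quantity is estimated.

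The size of the gain rests on an unstated ρ. For measurements a few hours apart ρ could be high, and at 0.9 the saving is only 5%.

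For dyspnoea and pain ratings a rank test is defensible, and the Protocol promises effect sizes and confidence intervals there. That weakens the case on those outcomes without removing the benefit of using their h0 values.

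Finally, a rule for choosing the test might sit in an analysis plan that is not shown. But the Protocol itself names the primary test as one of two, and pairs a stated mean comparison with a test that does not make it.

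**Conclusion.** The point holds as a recommended improvement, not as a defect of validity. Adjusting for baseline PCO2 would reduce the variance of the primary comparison by about 5% to 35%, assuming equal variances and ρ between 0.9 and 0.3. If the unadjusted test had 80% power, the adjusted one would have about 82% to 93.5%. With no ρ, SD, effect size or power in the Protocol, these figures show the order of the gain and are not a forecast.

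The mismatch between a stated mean reduction and an optional Mann-Whitney test rests on the wording alone and needs no assumption. Its consequence is an unfixed estimand, not a demonstrated loss of error control.

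**What to change.** Replace the either/or sentence with one primary analysis: a linear model of PCO2 at the primary time point on arm, with baseline PCO2 as covariate, by intention to treat at the two-sided 5% level. Report the adjusted mean difference with its 95% CI, and state that this does not depend on any normality check. Apart from sign, the same arm difference results whether follow-up PCO2 or its reduction is modelled, so the endpoint definition can stay as it is.

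Name the Mann-Whitney test on the reduction as a sensitivity analysis. This gives content to the sensitivity analyses that the Protocol promises for the primary outcome but does not describe.

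For comfort, dyspnoea and pain, use the same form of model with the h0 value as covariate.

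Which of h2 and h4 is the primary time point is a separate question and must be settled on its own.

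The cost is wording. Baseline PCO2 and the h0 ratings are already collected, the planned SPSS software fits the model, and the checklist at the front of the Protocol states that no patients have yet been enrolled.

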| Chronic obstructive pulmonary disease (COPD) is a major global health concern, ranking as the third leading cause of death worldwide [1]. Non-invasive ventilation (NIV) is a cornerstone therapeutic strategy for managing patients with severe exacerbations, particularly those with hypercapnic encephalopathy [3]. However, the efficacy of this |

technique is dependent on several factors. In fact, patient anxiety and discomfort, despite appropriate pressure settings and equipment, can lead to premature mask removal and excessive air leaks [4]. In recent years, there has been growing interest in applying music therapy in medical contexts, particularly in intensive care units. Recent studies have explored the potential benefits of music therapy in patients with acute respiratory failure requiring invasive mechanical ventilation [6–8]. Some studies have demonstrated positive effects of music therapy on anxiety, pain, analgesic use, delirium, and overall patient satisfaction [6,7,9,10]. Music therapy can also reduce agitation in confused patients, improve mood, and facilitate communication [6]. Within the context of NIV, music therapy may serve as a valuable non-pharmacological intervention. By enhancing patient acceptance and tolerance of the technique, music therapy can potentially improve the efficiency of NIV sessions [11]. There is limited literature on the impact of music therapy on NIV experience. To the best of our knowledge, no studies have yet examined the intra-session effects of music therapy on critically ill COPD patients undergoing NIV for acute exacerbation. By addressing the psychological and emotional challenges associated with NIV, music therapy could potentially improve patient acceptance, adherence to this technique and then clinical outcomes.

Objective(s) of the work:

to assess the impact of music therapy on the efficacy of NIV in patients with Acute Exacerbation of Chronic Obstructive Pulmonary Disease (AECOPD). We hypothesize that intra-session music therapy can improve NIV efficacy and tolerance in AECOPD compared to conventional care.

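### The repeated-measures step for PCO2 lists two times at which PCO2 is not scheduled, omits baseline, and looks only at change within groups

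*Protocol*

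**What the plan says.** **Measurement.** Under Primary Endpoint, the Protocol defines the outcome as baseline PCO2 (t0) minus the PCO2 "levels recorded at specific time points during the NIV session (h2, h4"), labelled t1 and t2. Under Secondary Endpoints, a denser schedule is set: "immediately after proper setup (5 minutes), and then at hourly intervals (h1, h2, h3, h4"). It covers respiratory rate, oxygen saturation, tidal volume, leak rate, heart rate, and systolic and diastolic pressure. PCO2 is not on that list.

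**Analysis.** Under Statistical analysis and expected results, the primary-endpoint paragraph has two steps.

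- The mean PCO2 reduction in the two arms "will be compared using a student t-test or Mann-Whitney U test, as appropriate".
- "Repeated measures analysis of variance (ANOVA) or a mixed-effects model approach" then "will be used to analyze within-group changes across time points (h1, h2, h3, h4").

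The secondary outcomes follow under their own lead-in. For the respiratory and cardiovascular parameters the plan is: "Differences between groups over time will be analysed using repeated measures ANOVA or mixed-effects models".

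**Hypothesis.** Under Objective(s) of the work, the trial's claim is that "intra-session music therapy can improve NIV efficacy and tolerance in AECOPD compared to conventional care".

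**The concern.** The second step of the primary-endpoint analysis does not match the endpoint it serves. It names times at which PCO2 is not taken, omits the baseline from which change is counted, and describes change within each arm although the hypothesis compares arms.

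The contrast matters most. Both arms receive NIV, so PCO2 may fall in both whatever music does. Separate within-arm p-values invite the argument that music works because the fall is significant in one arm and not in the other. That pattern can arise by chance when music has no effect.

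The first step does compare the arms, but it refers only to an endpoint PCO2, while the endpoint definition gives two. The step that explicitly spans several times, and could have settled how h2 and h4 are used, has no arm term.

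**Working it through.** The Protocol gives no figure on this point to reproduce. The check sets the sections side by side and then sizes the effect of the wrong contrast.

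**1. Times**

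| Time | PCO2 scheduled (Primary Endpoint) | Listed in the repeated-measures step |
|---|---|---|
| t0 | yes | no |
| h1 | no | yes |
| h2 | yes | yes |
| h3 | no | yes |
| h4 | yes | yes |

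Two of the four listed times have no PCO2: 2/4 = 50%. One of the three scheduled PCO2 times, the baseline, is not listed. The listed times are the hourly ones set for the seven secondary parameters.

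**2. Contrast**

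The PCO2 step names change within groups and no group or group-by-time term. The hourly secondary parameters are given differences between groups over time. As written, heart rate has a comparative longitudinal analysis and PCO2 does not.

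**3. What a within-arm test shows when music does nothing**

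From the Protocol: 38 patients per arm, two-sided 5% level. Assumed: normally distributed change scores, no music effect, and both arms improving by the same amount m, in SDs of the change score. The values of m are illustrative. Each row is 40,000 simulated trials.

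| m (SD) | Music arm significant within arm | Music significant, control not | Between-arm t-test significant |
|---|---|---|---|
| 0 | 4.9% | 4.6% | 5.0% |
| 0.2 | 22.7% | 17.6% | 5.2% |
| 0.32 | 48.7% | 25.3% | 5.1% |
| 0.5 | 85.5% | 13.0% | 4.9% |
| 0.8 | 99.8% | 0.2% | 5.0% |

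The third column agrees with theory. If each within-arm test has probability p of significance and the arms are independent, the chance of music significant and control not is p(1 − p). This is largest at p = 0.5: 0.5 × 0.5 = 25%. Disagreement in either direction is 2p(1 − p), at most 50%. At p = 0.95 it is 2 × 0.95 × 0.05 = 9.5%, of which half (4.75%) favours music.

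The within-arm result follows the improvement common to both arms. The between-arm test holds its 5% level throughout.

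**4. The unnamed time in the first step**

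The endpoint definition yields two reductions per patient, at h2 and at h4. If each were tested at 5% and either could be claimed, the chance of a false claim would be 1 − 0.95² = 9.75% were the two tests independent. They share a baseline and the same patients, so the figure would lie between 5% and 9.75%. The Protocol does not say that both would be tested; it leaves the choice open.

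**The case against.** **The trial already has a between-group primary test.** This stands. A reader might infer from the faulty sentence that the trial cannot show a music effect. The Protocol does not support that: the sentence just before it compares PCO2 reduction between arms. The defect is in the repeated-measures step, together with the unnamed time in the comparison.

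**The analysis could still be run.** This stands in part. A repeated-measures ANOVA on all four listed times has no PCO2 data for two of them, but a mixed model could be fitted to the h2 and h4 values. It would still lack baseline and an arm contrast as described.

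**The sentence may be a carry-over from the hourly parameters.** This is plausible: the time list matches theirs and the sentence does not repeat the word PCO2. It nevertheless sits in the primary-endpoint paragraph, before the secondary outcomes begin, and the hourly parameters have their own analysis. A slip there still needs correcting.

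**The risk from within-arm tests may be small.** This stands if PCO2 falls clearly in both arms, since both tests would then nearly always be significant. In that case the within-arm test is harmless only because it carries no information about music.

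**Other stronger readings.** A reader might infer that h1 and h3 values would be imputed, or extra arterial samples drawn. Nothing in the Protocol says so. A reader might also hold that repeated-measures ANOVA breaks the intention-to-treat basis by dropping incomplete patients. The same section offers a mixed model as the alternative, multiple imputation when missingness is significant, and sensitivity analyses, so that charge is not made out. Reading tidal volume and leak rate before the NIV session is a separate, minor matter about secondary outcomes.

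**Conclusion.** The point holds for the repeated-measures step of the primary-endpoint paragraph. Half of its listed times have no PCO2, baseline is missing, and it has no between-arm contrast, so it cannot address the comparative hypothesis. This rests on the text alone.

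The simulated sizes rest on the assumed common improvements and normal change scores. With no music effect, music significant and control not occurs in at most about 25% of trials, and in far fewer when both arms improve strongly.

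The between-group test of PCO2 reduction remains, so the trial is not without a valid comparison, but its time point is unnamed. A later statistical analysis plan might add detail, but the Protocol's times and contrast conflict with its own endpoint definition and should be corrected there. The Protocol's checklist states that no patients have yet been enrolled, so there is time to do so.

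**What to change.** Replace the repeated-measures sentence in the primary-endpoint paragraph with text to this effect:

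> PCO2 at h2 and h4 will be analysed with a mixed model for repeated measures, with arm, time and arm-by-time as fixed effects and t0 PCO2 as a covariate. Between-arm differences will be reported at each time with 95% confidence intervals. The between-arm difference at [one named time] is the single primary test. A t-test or Mann-Whitney comparison of the PCO2 reduction at that time is a sensitivity analysis.

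Three further changes go with it:

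- Remove h1 and h3 from the PCO2 analysis.
- Do not use within-group tests as evidence of a music effect. Change within each arm may be described.
- Reword the t-test or Mann-Whitney sentence to match, so that two primary tests do not compete. The sponsor chooses h2 or h4 as the primary time before any data are seen.

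The endpoint itself is unchanged. With t0 PCO2 as a covariate, the arm difference in PCO2 at a given time is the arm difference in PCO2 reduction with the sign reversed.

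The cost is a protocol amendment and one decision on the primary time. It changes the primary test as well as the wording, so it should be settled before enrolment. The t0, h2 and h4 samples already planned are enough.

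### Unplanned interventions are recorded as a number per session but tested as a category that is never defined; the test does not fit the endpoint, and the information lost depends on an unstated rate

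*Protocol*

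**What the plan says.** Protocol, Secondary Endpoints, first item: "The number of unplanned interventions required by caregivers during the NIV session will be documented". This is a count for each patient's session.

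Protocol, Statistical analysis and expected results, last item of the secondary outcomes list: "For categorical secondary outcomes (e.g., unscheduled interventions): comparisons between groups will be made using a chi-square test", with Fisher's exact test as the alternative. The same section says of such variables: "Categorical variables will be summarized as frequencies and percentages".

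The two sections use different words, unplanned and unscheduled. No other listed secondary endpoint fits the second word, so I read them as one endpoint. The protocol gives no cut-point, no grouping of the counts and no expected number of interventions per session.

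**The concern.** A chi-square or Fisher test needs categories, and the protocol defines none. The analyst would have to choose them: any versus none, some other cut, grouped counts, or every observed value as its own column. These choices can give different answers on the same data, and the text does not settle which applies.

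Each choice also costs something. Any versus none treats one intervention like six. The full table of values ignores their order and has sparse cells with 38 patients per arm. A test of this kind gives a P value but not the natural effect measure, the ratio of intervention rates. The protocol promises effect sizes with 95% confidence intervals for comfort and patient-reported outcomes, but not here.

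At stake is the trial's ability to show an effect on one of the secondary endpoints that bear on its stated hypothesis about tolerance of NIV.

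**Working it through.** **Inputs from the protocol.** "the final sample size is set at 38 patients per group" (Sample size); "randomly allocated in a 1:1 ratio" (Sampling procedure); "All statistical analyses will be conducted on an intention-to-treat basis at a bilateral 5% alpha risk" (statistical section). The total agrees: 2 × 38 = 76. The protocol states no figure for unplanned interventions, so there is nothing to reproduce for this endpoint. All means, rate ratios and dispersions below are assumptions.

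**Step 1: information kept by any versus none.** Let μ be the mean number per session. For Poisson counts, the Fisher information on log μ per patient is μ from the full count and μ²/(exp(μ) − 1) from any versus none. The fraction kept is

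μ / (exp(μ) − 1).

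For negative binomial counts with dispersion 1 the corresponding fraction reduces to 1/(1 + μ).

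| Mean per session | Kept, Poisson | Kept, neg. binomial (dispersion 1) |
|---|---|---|
| 0.25 | 88% | – |
| 0.5 | 77% | 67% |
| 1 | 58% | 50% |
| 1.26 | 50% | – |
| 2 | 31% | 33% |
| 3 | 16% | 25% |
| 5 | 3% | 17% |

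As an example, at μ = 2 the Poisson fraction is 2/(7.389 − 1) = 0.313. Near the null, 38 patients per arm then carry about as much information as 38 × 0.313 ≈ 12 patients analysed by their counts. At μ = 0.5 the equivalent is 38 × 0.771 ≈ 29. The loss passes one half at about 1.26 (Poisson) or 1 (negative binomial, dispersion 1).

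**Step 2: power by simulation.** The settings were 38 per arm, two-sided 5%, 2,000 trials per scenario (Monte Carlo standard error at most √(0.5 × 0.5/2000) ≈ 1.1 points) and an assumed rate ratio of 0.6. Chi-square is without continuity correction. The rate ratio is tested on the log scale with a variance taken from the observed spread of the counts.

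| Counts, control mean | Chi-square, any/none | Fisher, any/none | Chi-square, full table | Mann-Whitney | Rate ratio |
|---|---|---|---|---|---|
| Poisson, 0.5 | 25% | 18% | 15% | 26% | 27% |
| Poisson, 1 | 36% | 28% | 26% | 47% | 51% |
| Poisson, 2 | 43% | 33% | 41% | 75% | 79% |
| Poisson, 3 | 39% | 20% | 53% | 90% | 93% |
| Poisson, 5 | 9% | 1% | 71% | 98% | 99% |
| Neg. binomial (dispersion 1), 2 | 18% | 12% | 7% | 31% | 42% |

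At a Poisson control mean of 0.5, the gap between chi-square and the rate ratio is 27 − 25 = 2 points. At a mean of 2, count methods gain 75 − 43 = 32 to 79 − 43 = 36 points over chi-square.

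**Step 3: type I error.** With no true difference, over Poisson counts and negative binomial counts with dispersion 0.5 and 1, Mann-Whitney rejected in 4.2–5.6% of trials and the rate ratio in 4.8–6.4%. The gains are therefore not bought by a materially inflated error rate, though the rate ratio test is slightly liberal in some overdispersed settings. Fisher rejected in at most 3.2%, so part of its shortfall is its own conservatism rather than lost information.

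**The case against.** The strongest reply is that this is a one-line inconsistency on one secondary endpoint in a methods section marked as brief, and that a definition of the category could sit in a SAP that is not shown. That would answer a mere gap. It does not answer this point, because the protocol itself names the endpoint as categorical and assigns the test, and that does not fit the number it says will be recorded.

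Several stronger readings are tempting, and the documents do not support them.

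- **That most of the information is lost.** The protocol gives no intervention rate. If interventions are rare the loss is a minority, and chi-square on any versus none performs almost as well as Mann-Whitney. Quoting only Fisher's test would also exaggerate the gap, since chi-square is planned too.
- **That repeated events in one patient will be pooled as independent, understating the variance.** Nothing in the text says that events will be pooled by arm. A chi-square test can be run on per-patient categories.
- **That early stopping of NIV will look like success.** The background mentions premature mask removal, so unequal time at risk is conceivable. But assessments are scheduled to h4 for everyone, and no passage describes how session length varies or how stopping is counted. An offset for hours on NIV would not cleanly repair this either: that time arises after randomisation, may be affected by music, and may be cut short for reasons related to outcome.
- **That this is the main measure of tolerance.** It is listed first, but the protocol does not rank its secondary endpoints.

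It also stands that a negative binomial model is not the only remedy. Mann-Whitney recovers most of the power.

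**Conclusion.** The mismatch is certain from the text: a count is recorded, and an undefined category is tested. It deserves correction, because the planned test loses information however it is run on per-patient counts, and a better method costs almost nothing.

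The size is conditional. Under any versus none with Poisson counts, it runs from about 12% of the information at a mean of 0.25, through 23% at 0.5, to 97% at 5. A majority is lost only above roughly 1 to 1.26 interventions per session. The power figures rest on assumed means, a rate ratio of 0.6 and the chosen count distributions, none of which come from the protocol. The primary endpoint and the sample size of 38 per group are not affected.

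**What to change.** In the statistical section, take unplanned interventions out of the categorical item and state the following, using one term for the endpoint throughout:

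- The number of unplanned interventions per patient will be compared between groups by a rate ratio with 95% confidence interval, from a negative binomial model or a Poisson model with overdispersion or robust variance. At minimum, use the Mann-Whitney test already in the plan.
- The proportion of patients with at least one intervention will be reported descriptively.
- An analysis per hour on NIV, if wanted, will be a sensitivity analysis, with the caution that time on NIV is observed after randomisation and early stopping may be informative.

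The cost is a sentence or two of text and slightly more analysis work. The count is already to be documented, so the main analysis needs no new data. The sensitivity analysis would need NIV start and stop times on the data sheet. The protocol's checklist says that no patients have yet been enrolled, so the change can be made before any data exist.
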